**Fig. 2 Fig2:**
[figure not shown]
Cluster and evaluation village map in Alfadanga Upazila

A sampling frame of households with at least one eligible resident, aged over 30 years, within the evaluation villages will be generated, based on a study census completed in January 2020. A sample of 110 households will be selected using simple random sampling, with a random number generator in Stata SE 14. At the next stage, a single eligible adult will be selected from each sampled household, using simple random sampling. At each survey, a new sample of households and individuals will be generated with replacement from the same sampling frame, i.e. some individuals and households may be sampled more than once by chance. Individuals identified with intermediate hyperglycaemia in the baseline survey will be purposefully sampled for inclusion in subsequent surveys.

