**Methods:**

This is a stepped-wedge cluster randomised controlled trial, with integrated process and economic evaluations, conducted from March 2020 to September 2022. The trial will evaluate a community-based four-phase PLA cycle intervention focused on prevention and control of T2DM implemented over 18 months, against a control of usual care. Twelve clusters will be randomly allocated (1:1) to implement the intervention at project month 1 or 12. The intervention will be evaluated through three cross-sectional surveys at months 1, 12 and 24. The trial will be conducted in Alfadanga Upazila, Faridpur district, with an estimated population of 120,000. Clusters are defined as administrative geographical areas, with approximately equal populations. Each of the six unions in Alfadanga will be divided into two clusters, forming 12 clusters in total. Given the risk of inter-cluster contamination, evaluation surveys will exclude villages in border areas. Participants will be randomly sampled, independently for each survey, from a population census conducted in January 2020. The primary outcome is the combined prevalence of intermediate hyperglycaemia and T2DM, measured through fasting and 2-h post-glucose load blood tests. A total of 4680 participants provide 84% power to detect a 30% reduction in the primary outcome, assuming a baseline of 30% and an ICC of 0.07. The analysis will be by intention-to-treat, comparing intervention and control periods across all clusters, adjusting for geographical clustering.

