### Outcome

The primary outcome is the combined prevalence of intermediate hyperglycaemia (i.e. impaired fasting glucose and/or impaired glucose tolerance) and T2DM amongst adults aged 30 years or older, based on WHO definitions (Table 1) [20]. This is the same definition used in the DMagic trial.

**Table 1 Tab1:** WHO definition of normoglycaemia, intermediate hyperglycaemia and T2DM [20]

Definition	Diagnostic criteria
Normoglycaemia	Fasting plasma glucose ≤ 6.0 mmol/l
Intermediate hyperglycaemia	
Impaired fasting glucose	Fasting plasma glucose ≥ 6.1 mmol/l to < 7.0 mmol/l AND 2-h post-ingestion of 75 g glucose load plasma glucose < 7.8 mmol/l
Impaired glucose tolerance	Fasting plasma glucose < 7.0 mmol/l AND 2-h post-ingestion of 75 g glucose load plasma glucose ≥ 7.8 to < 11.1 mmol/l
Type 2 diabetes mellitus	Fasting plasma glucose ≥ 7.0 mmol/l OR* 2-h post-ingestion of 75 g glucose load plasma glucose ≥ 11.1 mmol/l

Secondary outcomes include the following: self-awareness of diabetes status, smoking prevalence, physical activity, mean population diastolic and systolic blood pressure, prevalence of hypertension (systolic blood pressure ≥ 140 mmHg or a diastolic blood pressure ≥ 90 mmHg or current treatment with antihypertensive medication), mean population body mass index, prevalence of overweight and obesity, mean population waist and hip circumference ratio, consumption of sugar, dietary diversity, knowledge of diabetes symptoms and complications, utilisation of diabetic services, psychological distress and ability to self-manage amongst diabetics. The cumulative incidence of T2DM amongst individuals with intermediate hyperglycaemia, identified during the survey at month 1 and followed up in subsequent surveys (at 12 and 24 months), will be calculated. Primary and secondary outcomes will be measured at months 1, 12 and 24 (Fig. 1).

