### Sample size

The sample size was calculated using a presumed baseline combined prevalence of intermediate hyperglycaemia and T2DM of 30%, an assumed exchangeable correlation structure across surveys for each cluster, and an estimated intra-cluster correlation of 0.07. A sample of 110 participants per cluster, per survey, will give 84% power at 95% confidence to detect a minimum of 30% relative reduction in disease prevalence to 21% or less. An additional 10% was added to the sample size to allow for non-response, resulting in a total target sample of 3960. We will, in addition, include individuals identified with intermediate hyperglycaemia in subsequent surveys. We estimate 360 individuals will be identified as having intermediate hyperglycaemia at baseline and included in the month 12 and 24 surveys. The sample size was calculated using Stata SE14.

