### Analysis

The primary analysis will be an intention-to-treat analysis, at the individual level, comparing the combined prevalence of intermediate hyperglycaemia and T2DM between intervention and control periods across all clusters. All participants sampled during intervention periods will be included in the primary analysis, regardless of their direct engagement with the groups. The analysis will be based on regression models that include fixed effects for intervention exposure, survey timing, and sociodemographic predictors, and random effects for geographical clustering and, where appropriate, individual and household clustering (e.g. if the same individual or household is randomly sampled in two surveys). Participants with missing data on the primary outcome will be excluded from the analysis, as we anticipate high levels of participation. All estimates of the intervention effects will be presented with 95% confidence intervals. Data analysis will be done blinded, and clusters will only be unmasked following the presentation of the primary results to the Trial Steering Committee.

Outcome data in the intervention condition are collected at 12 and 24 months after the intervention is first implemented (Fig. 1). The primary analysis will however estimate one effect of the intervention, which assumes the effect of the intervention is the same after 12 and 24 months. To explore this assumption, we a priori plan to report the estimated intervention effects at these two durations separately, fitting a model that includes two intervention duration indicators. Intuitively, we can see the midline data allow the intervention effect after 12 months relative to control to be estimated, and the endline data allow the effect after 24 months relative to 12 months to be estimated. Combining these two will give the effect of the intervention after 24 months relative to control. Assuming that the intervention effect is the same at 18 months, when the intervention activities are completed, and 24 months (i.e. it does not ‘tail off’ once groups no longer have a paid facilitator), then the 24-month effect can be interpreted as the ‘full’ intervention effect.

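### Baseline intermediate-hyperglycaemia cases are added purposively to both follow-up surveys, the primary prevalence analysis is not restricted to the random samples, and the abstract counts the added records towards the 84% power

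*Protocol article*

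**What the plan says.** All references are to the protocol article.

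- **Outcome:** "The primary outcome is the combined prevalence of intermediate hyperglycaemia (i.e. impaired fasting glucose and/or impaired glucose tolerance) and T2DM", in adults aged 30 or older. A person with intermediate hyperglycaemia at baseline therefore already has the primary outcome at that point. The same section gives a separate secondary outcome for these people, the cumulative incidence of T2DM over the later surveys.
- **Sampling:** "A sample of 110 households will be selected using simple random sampling" (per cluster), with one adult per household and a fresh draw at each survey. Then: "Individuals identified with intermediate hyperglycaemia in the baseline survey will be purposefully sampled for inclusion in subsequent surveys".
- **Sample size:** the 84% power is tied to 110 participants per cluster per survey, and the target is 3960. After that: "We will, in addition, include individuals identified with intermediate hyperglycaemia in subsequent surveys", and "We estimate 360 individuals will be identified as having intermediate hyperglycaemia at baseline and included in the month 12 and 24 surveys".
- **Analysis:** "All participants sampled during intervention periods will be included in the primary analysis, regardless of their direct engagement with the groups". The model has fixed effects for exposure, survey timing and sociodemographic predictors, and random effects for clustering. The article mentions no weight, cohort term or exclusion for the purposive group. Its example of repeat measurement is a person drawn at random twice.
- **Abstract, Methods:** "Participants will be randomly sampled, independently for each survey, from a population census conducted in January 2020", and "A total of 4680 participants provide 84% power to detect a 30% reduction in the primary outcome".

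**The concern.** The trial's hypothesis is a fall of at least 30% in population prevalence, and the cost per case prevented depends on that estimate. A simple random draw of households, with one adult from each, supports such an estimate. A group chosen because its members had part of the outcome at baseline does not. If that group is analysed together with the random draws at months 12 and 24, but is absent at month 1, the follow-up surveys no longer describe adults aged 30 and over. The treatment effect becomes a blend of the population effect and the effect in a selected high-risk group.

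The article does not say outright that this pooling will happen. But its inclusion sentence does not prevent it, its abstract total counts the purposive records towards the primary outcome, and its abstract description of the sampling is untrue of them. An analyst following the text could pool in good faith.

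**Working it through.** **1. The two totals.**
- Random sample: 110 × 12 clusters × 3 surveys = 3960, the target in the Sample size section.
- Purposive records: 360 × 2 follow-up surveys = 720.
- 3960 + 720 = 4680, exactly the abstract's total.
- Purposive share of each follow-up survey: 360 / (110 × 12 + 360) = 360/1680 = 21%, or 30 per cluster beside 110. Share of all records: 720/4680 = 15%.

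**2. Which total gives 84%?** Inputs from the article: prevalence 0.30 against 0.21, ICC 0.07, 12 clusters, six with exposure (0,1,1) and six with (0,0,1), and an exchangeable correlation. The 95% confidence is read as two-sided alpha 0.05. The Hussey–Hughes variance is

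Var = I·s²(s² + T·τ²) / [(I·U − W)s² + (U² + I·T·U − T·W − I·V)τ²]

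with I = 12, T = 3, U = 18, W = 0² + 6² + 12² = 180, V = 6×2² + 6×1² = 30.

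For 110 per cluster-survey, with individual variance from the control prevalence:
- s² = 0.30 × 0.70 / 110 = 0.001909
- τ² = (0.07/0.93) × 0.21 = 0.015806
- Numerator: 12 × 0.001909 × (0.001909 + 3 × 0.015806) = 0.001130
- Denominator: 36 × 0.001909 + 72 × 0.015806 = 1.2068
- Var = 0.000936, SE = 0.0306
- Power = Φ(0.09/0.0306 − 1.96) = Φ(0.98) = 83.7%

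The 84% is reproduced on the random sample alone. The result varies with the choice of individual variance and ICC convention:

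| Per cluster-survey | Power |
|---|---|
| 100 (responders, if 110 already holds the 10% allowance) | 80.1–86.8% (84.3% with averaged variance) |
| 110 | 83.7–89.7% |
| 130 (= 4680/36) | 89.1–93.8% |

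At 130 no variant comes down to 84%.

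**3. What pooling would do to the effect.** Let p be prevalence in the random sample and q the proportion of the purposive group still raised at follow-up. The article gives no q, so 50–80% is an assumption. Pooled prevalence = (110p + 30q)/140.

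- Control condition, p = 0.30: q = 0.50 gives 48/140 = 34.3%; q = 0.80 gives 57/140 = 40.7%.
- Intervention lowers p to 0.21 and leaves q unchanged: difference = 110 × 0.09/140 = 7.1 points, whatever q is. In relative terms this is 7.07/34.3 = 21% to 7.07/40.7 = 17%, instead of 30%.
- Both groups fall 30% in relative terms: difference = (9.9 + 30 × 0.3q)/140, which is 10.3 points at q = 0.50 and 12.2 at q = 0.80. The pooled relative reduction then stays at 30%; only the absolute difference changes.

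**4. Is there a false effect under the null?** A 4000-replicate simulation used generalised least squares on cluster-survey means. About 30% of each baseline sample was carried forward, with persistence of 50%, 70% or 90%. With survey effects in the model, the mean estimate under no effect was between −0.0005 and +0.0004. With a true −0.090, it was about −0.068 if the added group did not respond, and −0.103 to −0.131 if it had the same relative reduction.

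**5. How firm is 30 per cluster?** 360 = 0.30 × 1200, the combined prevalence applied to 100 per cluster, although only intermediate-hyperglycaemia cases are followed. The true number is probably lower. With 20 per cluster (illustrative), the figures become 9.9/130 = 7.6 points, and (9.9 + 20 × 0.3q)/130 = 9.9 to 11.3 points.

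**The case against.** The strongest reply is that the authors probably meant the random samples only. The inclusion sentence is chiefly an intention-to-treat statement: people who never attend a group still count. It names intervention periods only, so it is not a full definition of the analysis set. The Outcome section gives the followed-up cases a secondary outcome of their own. The Sample size section calculates power on 110 per cluster per survey and brings these cases in afterwards. The repeat-sampling example concerns chance repeats, which suits a model built for random draws. A detailed analysis plan is promised, and analysis sets are usually defined there.

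Most of this stands as evidence of intent. A reader might infer that the article fixes a pooled primary analysis; the text does not go that far. A reader might also infer that the added cases would produce a spurious benefit or harm. The documents do not support that either, because the cases join both sequences at both follow-ups and survey timing is in the model.

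The reply does not dispose of what is stated. The abstract says 4680 participants provide the power for the primary outcome, which counts the purposive records. It also describes every participant as independently randomly sampled, which the Sampling section contradicts. Those are statements, not details left to a later document.

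**Conclusion.** The point holds as an unresolved analysis set together with a wrong power attribution. The article leaves open whether about 21% of each follow-up survey, selected on a component of the primary outcome, enters the primary comparison, and its abstract points towards inclusion. The 84% belongs to the 3960 random participants, not to 4680.

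If the records were pooled, the harm would be to what is estimated, not to the type I error in expectation. For a true 9-point reduction the estimate would be about 7.1 points with no response in the added group. It would be about 10 to 12 points with a 30% relative fall and 50–80% persistence. Persistence and response are assumptions, complete non-response is an extreme bound, and 30 per cluster is probably high, so these figures show the possible scale and are not a forecast. Even the direction depends on quantities the article does not give. Means and prevalences among the secondary outcomes are open to the same mixing; its size there was not calculated.

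**What to change.** 1. State that the primary analysis, and every secondary analysis of a population prevalence or mean, uses only the randomly drawn sample at each survey. A baseline intermediate-hyperglycaemia case counts in a later survey only if drawn by chance in that survey.
2. Carry a flag in the data that separates random from purposive records, and use the purposive records only for the cumulative incidence of T2DM.
3. Correct the abstract so that the 84% is attached to 3960 random participants, with the 720 follow-up records stated separately and the description of random sampling limited to the random draws.

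The cost is a sentence in the analysis-set definition, a sampling flag and a corrected abstract statement. No extra data are needed, and no planned power is lost because the 84% already rests on the random sample.

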### Sample size

The sample size was calculated using a presumed baseline combined prevalence of intermediate hyperglycaemia and T2DM of 30%, an assumed exchangeable correlation structure across surveys for each cluster, and an estimated intra-cluster correlation of 0.07. A sample of 110 participants per cluster, per survey, will give 84% power at 95% confidence to detect a minimum of 30% relative reduction in disease prevalence to 21% or less. An additional 10% was added to the sample size to allow for non-response, resulting in a total target sample of 3960. We will, in addition, include individuals identified with intermediate hyperglycaemia in subsequent surveys. We estimate 360 individuals will be identified as having intermediate hyperglycaemia at baseline and included in the month 12 and 24 surveys. The sample size was calculated using Stata SE14.

### Data collection

Data will be collected through three cross-sectional surveys at months 1, 12 and 24 (Fig. 1), by six pairs of fieldworkers (one male and one female) with three supervisors. Data collectors with completed secondary education will be recruited locally and selected following written assessment and interview. All fieldworkers will undergo 2 weeks of training, including consent, survey methods and physical measurements, followed by 1-week supervised field practice in villages outside of the study area. During training and field practice, survey tools will be piloted and revised. Within each village, teams will be aided by a village assistant, who will receive a daily payment to coordinate communication with study participants and assist data collectors. They will inform sampled individuals about the time and location of data collection, including the need to fast overnight. A convenient location within the village will be selected for the blood and anthropometric measures, and the collection of questionnaire data will take place at the respondent’s home. All participants will be provided with verbal and written study information prior to taking part in anthropometric assessments and surveys, and data will only be collected following signed consent.

Individual, interviewer-administrated questionnaires will collect information on demographic and socio-economic characteristics, risk behaviours, diabetes awareness indicators, health-seeking and costs of care. This questionnaire will be adapted from the WHO Stepwise tool [21] and the 2014 Bangladesh Demographic and Health Survey [14] and will include GAD-7 and PHQ-9 for mental health assessment [22, 23] and an adapted Appraisal of Diabetes Scale [24]. Blood pressure will be measured using the OMRON HBP 1100 Professional Blood Pressure Monitor (Kyoto, Japan). Two measurements will be taken with a 5-min interval, and the average will be taken for analysis. Height, weight, and waist and hip circumference will be measured, asking respondents to wear only light clothing and removing shoes. Blood glucose will be measured using the OneTouch Verio Flex Glucometer (Lifescan, Inc., Milpitas, CA 95035) in mmol/l, from the whole blood obtained by finger prick. Participants will be tested following an overnight fast of 8–12 h and then again 2-h after receiving a 75-g glucose load dissolved in 250 ml of water. In self-reported diabetics, we will take a random blood glucose measurement only.

Data will be collected using ODK Collect on Android tablets and downloaded via USB onto field supervisor’s laptops and shared via a secure cloud server. Clusters, villages, households and individuals will be linked using unique study identifiers. Personal identifiable data will be collected in order to identify the sampled individuals in the community during surveys; however, these will be removed following cleaning for analysis and archiving. Data quality will be promoted through pilot testing of data collection tools, in-built range and logic checks, supervisor observation of data collection and concurrent data checking, with errors sent back to the field team for verification.

### Analysis

The primary analysis will be an intention-to-treat analysis, at the individual level, comparing the combined prevalence of intermediate hyperglycaemia and T2DM between intervention and control periods across all clusters. All participants sampled during intervention periods will be included in the primary analysis, regardless of their direct engagement with the groups. The analysis will be based on regression models that include fixed effects for intervention exposure, survey timing, and sociodemographic predictors, and random effects for geographical clustering and, where appropriate, individual and household clustering (e.g. if the same individual or household is randomly sampled in two surveys). Participants with missing data on the primary outcome will be excluded from the analysis, as we anticipate high levels of participation. All estimates of the intervention effects will be presented with 95% confidence intervals. Data analysis will be done blinded, and clusters will only be unmasked following the presentation of the primary results to the Trial Steering Committee.

Outcome data in the intervention condition are collected at 12 and 24 months after the intervention is first implemented (Fig. 1). The primary analysis will however estimate one effect of the intervention, which assumes the effect of the intervention is the same after 12 and 24 months. To explore this assumption, we a priori plan to report the estimated intervention effects at these two durations separately, fitting a model that includes two intervention duration indicators. Intuitively, we can see the midline data allow the intervention effect after 12 months relative to control to be estimated, and the endline data allow the effect after 24 months relative to 12 months to be estimated. Combining these two will give the effect of the intervention after 24 months relative to control. Assuming that the intervention effect is the same at 18 months, when the intervention activities are completed, and 24 months (i.e. it does not ‘tail off’ once groups no longer have a paid facilitator), then the 24-month effect can be interpreted as the ‘full’ intervention effect.

We will also explore subgroup analyses, by socio-economic status, gender, age and for both intermediate hyperglycaemia and T2DM separately. As we have a small number of clusters involved in the trial, we are considering the use of random effects models with a correction for the modest number of clusters. This is an active area of methodological research, and a detailed final analysis plan will be written before the analysis begins.

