**Fig. 1 Fig1:**
[figure not shown]
Stepped-wedge trial design

The trial clusters will be randomly allocated, with a 1:1 ratio, to implement the intervention at either project month 1 or 12. The intervention will be evaluated with three cross-sectional surveys, at project months 1 (baseline), 12 (midline) and 24 (endline). The trial intervention period is planned to run for 30 months, from March 2020 to September 2022 (Fig. 1).

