### Randomisation

Due to the nature of the intervention, communities cannot be blinded to cluster allocation. Informed community consent will be taken through discussions with local leaders. Thereafter, clusters will be randomly allocated at a public meeting in the presence of traditional leaders and representatives from communities. The name of each cluster will be written on pieces of paper and folded uniformly by study staff, placed into a container and then drawn by a community representative. The clusters will be numbered in the order they are drawn, with clusters 1–6 implementing the intervention at month 1 and clusters 7–12 at month 12. The randomisation process will be filmed, with the consent of those present, to document the procedure.

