### Number of sequences

Given the considerations about the timing of steps and project duration, we explored designs with 2, 3 and 4 sequences and having steps at 3 months, 6 months, 9 months or 12 months after the first implementation of the intervention—all scenarios feasible within 36 months. Based on the DMagic process evaluation, we reasoned that the community meeting at month 10 in the PLA cycle is an important milestone when groups start to implement strategies and when we might realistically expect to observe changes in population-level knowledge and behaviours. We therefore projected that some impact may be measured by month 12 of the intervention, but is less likely before. We discussed conducting the community meeting earlier in the PLA cycle, but had concerns about deviating from the effective DMagic intervention, and process data suggested groups need this initial period for problem analysis and building collective consciousness. We also hypothesised that the intervention effect may be larger beyond the end of the planned 18-month delivery, than at 12-months, given longer exposure to the intervention. Setting a 12-month period before expecting measurable intervention effects, designs with three or more sequences and hence four or more data collection surveys would have meant excluding clusters from intermediate surveys (or from the primary analysis) which had more recently implemented the intervention.

We therefore opted for the two-sequence design as the most pragmatic balance, estimating an overall (average) primary intervention effect and also the intervention effect after 12 months (6 months before completion) and 24 months (6 after completion), relative to control. Our major concern is that finding no effect may be a design artefact if PLA takes the full 18 months to work or effects are not sustained. If we assume that it takes 6 months for diabetes status to change, the measured intervention effect at 24 months should reflect the complete intervention exposure at 18 months. We will therefore give emphasis to the impact at 24 months, if its seen to be larger than the impact after 12 months. We acknowledge however that our power to estimate the 24-month effect will be lower than for the primary effect. These pre-planned analyses of differential effects during the intervention period should provide important insights into the mechanisms and appropriate timeframe for intervention implementation in further scale-up.

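### The single-effect primary estimate is not an average of the 12- and 24-month effects: it weights the 24-month effect negatively, so it lies outside both effects whenever they differ

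*Protocol article*

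**What the plan says.** Randomisation has "clusters 1–6 implementing the intervention at month 1 and clusters 7–12 at month 12". Surveys take place at months 1, 12 and 24. The early sequence is therefore observed under control, after 12 months and after 24 months of intervention; the late sequence under control, control and after 12 months.

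The Analysis section specifies "fixed effects for intervention exposure, survey timing, and sociodemographic predictors, and random effects for geographical clustering", and says that the primary analysis will "estimate one effect of the intervention, which assumes the effect of the intervention is the same after 12 and 24 months". To explore that assumption it plans a model with two duration indicators. It explains that midline identifies the 12-month effect and that endline identifies the 24-month effect relative to the 12-month effect.

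The Discussion (Number of sequences) describes the primary analysis as "estimating an overall (average) primary intervention effect". The same subsection states: "We also hypothesised that the intervention effect may be larger beyond the end of the planned 18-month delivery, than at 12-months". It projects some impact by month 12, worries that a null result could come from the design if the intervention needs the full 18 months to work, and will emphasise the 24-month result if it turns out larger. It concedes lower power for that result.

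**The concern.** A reader told that the primary estimate is an average will take it to lie between the 12- and 24-month effects. At endline, however, every cluster is under intervention. The 24-month effect enters the data only through the endline difference between sequences, which is the 24-month minus the 12-month effect. A single-effect model takes that difference to be zero apart from cluster noise and subtracts part of it from the midline contrast. A later gain then counts against the intervention in the headline result, and the stated power applies only if there is no such gain. The trial is meant to inform policy on population-level prevention, so the meaning of its primary estimate matters.

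**Working it through.** **Inputs (Sample size, Randomisation, Analysis).** Six clusters per sequence; three surveys; "presumed baseline combined prevalence of intermediate hyperglycaemia and T2DM of 30"%; a fall to 21% (9 points); ICC 0.07, exchangeable across surveys; two-sided 5%. Since 12 × 3 × 110 = 3960, the 110 per cluster and survey already contains the 10% non-response allowance, leaving about 100 analysed.

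**Estimator.** Let D0, D1, D2 be the early-minus-late differences at baseline, midline and endline. Let τ² be the between-cluster variance and v the within-cluster variance divided by the number per cell. Under a single effect, D0 and D2 have expectation zero, so the generalised least squares estimate is D1 minus its best prediction from D0 and D2:

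estimate = D1 − c(D0 + D2), with c = τ²/(2τ² + v).

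On the ICC scale, c = 0.07/(0.14 + 0.93/100) = 0.07/0.1493 = 0.469.

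**Reproducing the stated power.** With total variance 0.30 × 0.70 = 0.21, τ² = 0.0147 and v = 0.21 × 0.93/100 = 0.001953. The variance is (1/3)[τ²(1 − 2c)² + v(1 + 2c²)] = (1/3)(0.000057 + 0.002812) = 0.000956, so SE = 3.09 points. For 9 points, 9/3.09 − 1.96 = 0.95, giving 83% power against the stated 84%. With the variance taken at p = 0.255 it is 86%.

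**What the estimate targets.** Write d12 and d24 for the two effects. The expectations of D0, D1 and D2 are 0, d12 and d24 − d12. Hence

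E(estimate) = d12 − c(d24 − d12) = (1 + c)d12 − c·d24 = 1.47 d12 − 0.47 d24.

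This is zero at d24/d12 = 1.469/0.469 = 3.1 and has the wrong sign beyond that.

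**Illustrations.** The documents give no growth pattern, so these pairs are assumptions (reductions in points; 100 per cell, p = 0.30; normal test).

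| 12 / 24 months | Simple average | Primary estimate | Power |
|---|---|---|---|
| 9 / 9 | 9.0 | 9.0 | 83% |
| 8 / 9 | 8.5 | 7.5 | 68% |
| 6 / 9 | 7.5 | 4.6 | 32% |
| 4.5 / 9 | 6.75 | 2.4 | 12% |
| 3 / 9 | 6.0 | 0.2 | 3% |
| 0 / 9 | 4.5 | −4.2 (apparent harm) | – |
| 9 / 4.5 | 6.75 | 11.1 | 95% |

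**Sensitivity of the 24-month weight.** It is −0.33 at ICC 0.01 (exchangeable). At ICC 0.07 it is −0.41 with cluster autocorrelation 0.8 and −0.31 with 0.5. Lowering both shrinks it further (−0.22 at ICC 0.01 with correlation decaying at 0.5). It reaches zero only at ICC 0. Across the correlation structures tried at ICC 0.07, the null ratio runs from 3.1 to 4.3.

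**Logistic check.** A random-intercept logistic simulation (300 runs per scenario, true 24-month OR 0.62) gave a single OR of 0.87, 0.99 and 1.25 when the 12-month effect was one half, one third and none of the 24-month log-odds effect. That agrees with the linear result.

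**Two-duration model.** With r = τ²/(τ² + v) = 0.883, set e1 = D1 − rD0 and e2 = D2 − rD0. Then d12 is estimated by e1, d24 by e1 + e2, and the simple average by e1 + e2/2. The SEs are 3.50, 6.00 and 4.59 points. Power for 9 points is 73%, 32% and 50% at p = 0.30, and 77%, 35% and 54% at p = 0.255.

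**The case against.** The protocol is open about much of this. It states the equal-effect assumption, commits in advance to the two-duration model, explains which survey identifies which effect, admits lower power at 24 months and warns that a null might come from the design. Readers will see unbiased duration-specific estimates beside the primary one. If the effect is constant, the single-effect model is unbiased and the most efficient choice, and every alternative loses power. All of that stands. None of it tells the reader that the primary estimate can fall outside the range of the two effects, and calling it an average says the opposite.

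A reader might go further and infer that a growing effect will be reported as null or harmful, or that the investigators expect a reversed sign. The documents do not support that. They say only that the later effect may be larger, without a size, and that some impact may be seen by month 12. Modest growth such as 8 to 9 points only attenuates the estimate. The wrong-sign case corresponds to the separately stated worry that the full 18 months are needed, which is a concern and not the projected scenario.

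Nor does it follow that the 12-month effect must become primary. It falls six months before the cycle ends, and the Analysis section treats the 24-month effect as the full one, provided that the effect holds up after month 18.

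**Conclusion.** The point holds. Describing the single-effect estimate as an average is wrong whenever the 12- and 24-month effects differ. At the protocol's inputs the weights are about +1.47 and −0.47, and the negative sign persisted in every setting tried with a positive ICC. Growth pulls the estimate below both effects and fading pushes it above both. Whether the result is mild attenuation, a null or a reversal depends on the amount of growth, which the documents do not give. The 84% power is reproducible (83–86%) but conditional on a constant effect, an assumption the protocol itself questions.

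The calculation rests on cluster-period means on a linear scale, about 100 analysed per cell and a normal reference distribution. It leaves out sociodemographic covariates, household or repeat-individual effects and the small-sample correction under consideration. Such a correction would lower all the powers shown.

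**What to change.** - Delete the description of the primary estimate as an overall or average effect.
- State that the single-effect estimate and the 84% power are valid only if the effect is constant from 12 to 24 months.
- Base the main conclusion on the two-duration-indicator model that is already planned. The investigators should fix its estimand (12-month, 24-month or their simple average) before analysis, replacing the rule that emphasises 24 months only if that effect looks larger.
- Report the single-effect model only alongside it, labelled as the constant-effect analysis.

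No new data are needed, but this is a change in what the headline result estimates, and its price should be stated. For a 9-point effect at 100 per cell, power is about 73–77% for the 12-month effect, 50–54% for the simple average and 32–35% for the 24-month effect, against 83–86% for the single-effect model. The choice among the three is a trade-off between power and relevance to the completed intervention. It belongs to the investigators and can be recorded in the detailed analysis plan that the article promises before analysis begins.
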